### Limitations

As this project is performed at different surgical centers in 5 countries across Europe, procedure and documentation characteristics may vary. Thus, the data set has to be limited to a common set of data frequently reported by all sites.

### Statistical Analysis

Assuming a mean *S. aureus* SSI rate of 1% [5], incidence rates can be determined with a 95% CI of plus or minus 0.5% by observing 1500 surgical procedures. Therefore, at least 15 centers will be included in the analysis, resulting in 90,000 to 150,000 observed patients. Assuming an incidence rate of *S. aureus* SSI of 1.5% in a population of 150,000, 2250 cases will be matched to 2250 controls.

Data will first be analyzed for missing values. We will perform a qualified evaluation of missingness mechanisms for each variable with more than 1% missing values. In case data are missing completely at random, patients with the missing value will be excluded from that respective analysis step (complete record analysis). For values not missing at random, multiple imputation using chained equations will be performed and compared to a complete record analysis for improved robustness of results. We will perform in-depth descriptive statistics of all parameters observed. Country-based and institution-based incidence rates will be determined for each procedure (eg, ventral hernia repair) and each category (eg, vascular surgery). For each incidence rate, the 95% CIs for a binominal proportion will be calculated. Costs will be calculated for both procedures and categories. Accounting for the usually non-normal distribution of costs in medical settings, statistical analyses (eg, CI construction) will be carried out using non-parametric bootstrap procedures. Reported SSI rates and cost will be further stratified by depth of SSI (eg, superficial, deep). Association between major cost drivers and SSI occurrence, as well as overall costs and SSI occurrence, will be determined using bootstrapped t tests.

Multivariable regression analysis will be used to confirm significance of SSI occurrence for overall treatment costs.

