### Rationale

Active, prospective SSI surveillance lowers SSI rates [13]; therefore, unbiased SSI rates should be determined by retrospective, non-interventional studies. This cohort study will sample a large percentage of the surgical population and thereby generate representative data. For the selection process and documentation of the overall cohort, we will limit data items to those that are generally available in electronic form, thus facilitating the sampling of an adequately sized and complete cohort with comparably low effort. Feasibility analysis of candidate study centers will assess center capability for electronic data provision. If needed, single data items may be waivered during the selection process. In this case, these data items would instead be documented as part of the nested case-control study.

The nested case-control part of this study is necessary to generate data required for outcomes and cost analyses, as most centers will not have electronic records sufficiently detailed to allow this analysis for the whole cohort. The approach avoids bias that has been introduced, for example by relying on reimbursement data to estimate costs [14], and thus describing the SSI price rather than its cost. Therefore, the best possible approach to an accurate, precise cost analysis is manual documentation by on-site medical personnel (eg, study nurses). Documentation must comprise relevant cost drivers of SSI cases and well-matched controls to allow analyses of incremental costs caused by SSI. On-site medical personnel would receive appropriate electronic case report form (eCRF) training prior to commencing documentation. In addition, manual data capturing allows concomitant plausibility checking.

Nesting the case-control study within a cohort ensures generalizability of the case-control results to the respective center as well as the cohort and, by means of a representative cohort, to the overall surgical population in Europe.

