#### Data Collection

##### Cohort

The following variables will be collected from EHRs for descriptive purpose only: (1) age by category; (2) sex; (3) BMI; (4) comorbidities (International Statistical Classification of Diseases and Related Health Problems [ICD-10] codes); (5) diabetes; (6) type of procedure; (7) duration of procedure; (8) occurrence of SSI related to observed procedure within 90 days, including date of diagnosis; (9) wound class.

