#### Primary Analysis

The primary objective of this study is to determine the overall and procedure-specific incidence of *S. aureus* SSI in Europe. The primary analysis will consist of calculating the incidence using 95% CIs.

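### The exclusion box and the analysis section give conflicting rules for values missing completely at random, and chained-equation imputation is assigned, as written, to data not missing at random while data missing at random have no rule

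*Protocol article*

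**What the plan says.** Two places in the Protocol article deal with incomplete records.

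- **Textbox 2 (inclusion and exclusion criteria)** lists cases whose missing data are classed as missing completely at random (MCAR) among the exclusions from the study. It names no field.
- **Statistical Analysis** starts with a screen: "We will perform a qualified evaluation of missingness mechanisms for each variable with more than 1% missing values". It then has two branches. The first: "In case data are missing completely at random, patients with the missing value will be excluded from that respective analysis step". The second: "For values not missing at random, multiple imputation using chained equations will be performed and compared to a complete record analysis for improved robustness".

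Three other statements bear on this. Primary Analysis says: "The primary analysis will consist of calculating the incidence using 95% CIs"; no covariate model is named. The Cohort data list, which includes BMI, comorbidities, duration and wound class, opens with: "The following variables will be collected from EHRs for descriptive purpose only". The Rationale allows centers some latitude: "If needed, single data items may be waivered during the selection process"; a waived item is then documented in the nested case-control part instead.

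**The concern.** **Denominator.** A patient with a known procedure and known SSI status but no recorded BMI is outside the study under Textbox 2 and inside the incidence analysis under Statistical Analysis. Both rules cannot be followed. MCAR also describes a mechanism, not a patient. It cannot be read off one record at eligibility, and observed data cannot confirm it.

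**Imputation.** Standard chained-equation imputation assumes that data are missing at random (MAR) given the variables in the model. The text assigns it to values not missing at random (MNAR) and gives MAR no rule. Yet MAR is a pattern this design can be expected to produce: at a center with a waived item, who has the value depends on center and on selection into the case-control part, both of which are observed.

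At stake are the size of the primary cohort, the precision of procedure-specific rates, the number of cases for the cost analysis, and the weight a reader can give to the planned robustness comparison.

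**Working it through.** **1. The plan's own figures.** Precision at a 1% rate: n = 1.96² × 0.01 × 0.99 / 0.005² = 1,522 (rounded up), against the stated 1,500. Conversely, 1,500 procedures give ±1.96 × √(0.01 × 0.99 / 1,500) = ±0.50 points. Cases: 1.5% × 150,000 = 2,250, as stated.

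**2. What incidence needs.** Country and institution are known by design. Overall and procedure-specific incidence otherwise need procedure type and SSI status. Age, sex, ASA score, BMI, duration and diabetes enter the matching, not the incidence.

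**3. Loss if Textbox 2 is applied to whole patients.** The document gives no missingness rates, so this is an illustration. Take the seven matching covariates in Secondary Analysis, each independently MCAR in a share m of patients. Share lost = 1 − (1 − m)^7.

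| m | Share lost | Kept of 150,000 | Cases kept of 2,250 | Half-width, stratum of 1,500 |
|---|---|---|---|---|
| 1% | 6.8% | 139,810 | 2,097 | ±0.52 |
| 2% | 13.2% | 130,219 | 1,953 | ±0.54 |
| 5% | 30.2% | 104,751 | 1,571 | ±0.60 |

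One of the seven is procedure type, which procedure-specific incidence does need. For the other six alone the loss is 5.9%, 11.4% or 26.5%. Under the step-wise rule, gaps in those six cost the incidence analysis nothing.

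**4. Bias in incidence.** Under true MCAR, infected and uninfected cohort members are removed in the same proportion, so incidence is unchanged in expectation. Bias needs a mechanism wrongly judged MCAR, and its direction follows the assumption. With a true rate of 1.0%:

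- Records 95% complete in infected and 80% in other patients: 0.01 × 0.95 / (0.01 × 0.95 + 0.99 × 0.80) = 1.19%.
- The reverse: 0.01 × 0.80 / (0.01 × 0.80 + 0.99 × 0.95) = 0.84%.

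**5. Imputation under each mechanism.** An illustrative simulation used 150,000 patients, 10 replicates, about 20% of BMI missing, and 10 imputations from a linear regression on age, duration and SSI status, as in one chained-equation step. In the MAR setting, missingness depended on age and SSI status; in the MNAR setting, lower BMI was more often missing.

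| Mechanism | True mean BMI | Complete records | Imputation |
|---|---|---|---|
| MCAR | 27.00 | 27.00 | 27.01 |
| MAR | 27.00 | 27.08 | 27.00 |
| MNAR | 27.01 | 27.85 | 27.84 |

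Imputation removes the bias under MAR. Under MNAR the two methods agree with each other and both are about 0.8 too high. In the same MAR setting, restricting to complete records moved incidence from 1.22% to 0.80%; under MCAR it stayed at 1.22%. The target here is a mean, not a planned estimand, so this shows only that agreement can coexist with bias.

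**The case against.** **The phrase may be loose wording.** Set beside the MCAR branch, not missing at random may simply mean not missing completely at random. Imputation would then fit the MAR part and the repair would be a word or two. This is plausible and limits the imputation point to what the sentence says. It does not remove it: as printed the phrase names MNAR, and an analyst following it literally would misapply the method.

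**The analysis rule already protects incidence.** Under step-wise exclusion no one leaves the denominator for a missing BMI. Textbox 2 names no field and could be meant for missing procedure or SSI status. This stands as a possible reading, but nothing in the text restricts the exclusion in that way, so the conflict remains.

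**A reader might infer that the primary incidence is biased upward.** The documents do not support this. True MCAR removal of cohort members does not bias a proportion, and step 4 gives shifts both ways under equally arbitrary assumptions. The word for those excluded is ambiguous: Detection of *S. aureus* Surgical Site Infection uses it for cohort members, Sample Size for infected patients. If only infected patients were removed, incidence would fall even under MCAR, but the text does not establish that reading.

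**A reader might also infer a loss of tens of thousands of patients.** That requires the assumed 5% in all seven fields, age and sex included, whereas the data set was limited to items generally available electronically. Even then about 104,750 remain, within the planned 90,000 to 150,000, and overall precision moves only from ±0.050 to ±0.060 points. The cost falls on smaller procedure strata and on the number of cases.

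**Complete-record analysis is not always biased under MNAR.** If a covariate's missingness does not depend on the outcome given the covariates, complete-record regression can be consistent. For the planned multivariable cost regression the comparison may therefore be informative. The supportable claim is only that agreement does not by itself show robustness.

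**Analysis detail may sit in the SAP.** Figure 2's legend lists a SAP that is not shown, so the absence of an MNAR method or an imputation model is not the point. The stated rules are.

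**Conclusion.** Two stated rules need correction. First, Textbox 2 and Statistical Analysis contradict each other on MCAR gaps and lead to different primary denominators. If cohort members are meant and the mechanism is truly MCAR, whole-patient exclusion costs precision and cases without bias. Bias in either direction arises if the mechanism is misjudged, which observed data cannot rule out. The size is unknown; 7%, 13% or 30% of patients is an illustration that rests on seven independent fields missing at 1%, 2% or 5%.

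Second, the imputation sentence as written assigns a MAR method to MNAR data and leaves MAR without a rule. Loose wording is a likely explanation. The documents support neither a demonstrated bias in the primary endpoint nor a claim that the complete-record comparison is worthless.

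**What to change.** 1. Delete the MCAR line from the exclusion criteria in Textbox 2. State that every patient with known procedure and SSI status enters the incidence analysis, whatever other fields are missing.
2. Reword the imputation sentence so that chained-equation imputation applies to covariates that are not MCAR and are treated as MAR in the matching and cost analyses, with complete-record analysis kept as a comparison.
3. Where MNAR is suspected, use a delta-adjusted sensitivity analysis and do not rely on that comparison alone. The detail can sit in the SAP.

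The cost is one deleted line, a few sentences of wording and modest extra analysis. No additional data are needed.

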**Methods:**

A retrospective, multinational, multicenter cohort study (*Staphylococcus aureus* Surgical Site Infection Multinational Epidemiology in Europe [SALT] study) with a nested case-control part will be conducted. The study will include all surgical procedures at a participating center in order to prevent selection bias and strengthen the understanding of SSI risk by determining the incidence for all common surgical procedures. Data will be assessed in the cohort population, including 150,000 adult patients who underwent any surgical procedure in 2016, and the case-control population. We will match patients establishing *S. aureus* SSI 1:1 with controls from the same center. Data on demographics, surgery, and microbiology will be exported from electronic files. More detailed data will be captured from the case-control population. The SALT study will include 13 major or academic surgical centers in Europe, comprising 3 in France, 4 in Germany, 2 in Italy, 3 in Spain, and 1 in the United Kingdom. Sites were selected using a feasibility questionnaire.

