## Introduction

### Background

Surgical site infections (SSIs) are among the most common hospital acquired infections and constitute an important quality criterion in health research [1,2]. The incidence of SSIs in certain indicator procedures is the subject of ongoing surveillance efforts in hospitals and health care systems around the world [1,3,4]. However, SSI rates vary markedly within surgical categories and are poorly represented by routinely monitored indicator procedures such as mastectomy, upper limb amputation, or inguinal hernia surgery [4]. Therefore, relying on indicator procedures to estimate the overall burden of SSIs is imprecise and introduces bias as hospitals may take special precautions to achieve lower SSI rates in indicator procedures. *Staphylococcus aureus* (*S. aureus*) is the most common cause of SSIs, as recently confirmed by a Europe-wide point-prevalence study conducted by the European Centre for Disease Prevention and Control (ECDC) [5].

Treatment of *S. aureus* infections is challenging due to the emergence of multi-drug resistant strains such as methicillin-resistant *S. aureus* (MRSA). To better plan future trials on new treatment strategies, knowledge on incidence and risk factors is of utmost importance.

Currently available data suggest that while the overall SSI rate and the proportion of SSIs caused by *S. aureus* vary, the absolute *S. aureus* SSI rate is similar for different procedures. Focusing on *S. aureus* SSIs, we aim to demonstrate that the *S. aureus* SSI rate is independent of the procedure performed and rather a consequence of cutaneous incisions. Such a demonstration would amount to a paradigm shift and allow future prevention studies to proceed differently.

SSIs are associated with poor outcome, prolonged hospitalization, and increased treatment costs [6]. Estimated excess treatment costs range between US $ 1000 to $20,000 [6-10]. Treatment costs depend, among other factors, on the depth of SSI (superficial, deep, or organ space) and the prior surgical procedure. However, the exact treatment costs remain unknown, as previous estimates are based on limited data from single institutions [9], provider networks [11], or highly aggregated data from surveillance programs [7]. Due to this heterogeneous data source, prior cost estimates for Europe show a wide range of results [12].

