With SSI rates being the primary endpoint, SSI detection methodology is crucial in this study. Prior studies and surveillance effort, if specifying detection methodology at all, are usually limited to the analysis of administrative code data [14,15]. However, a recent publication demonstrated that using bacteriological data is superior and combining both—administrative and bacteriological data—could be even more advantageous [16]. In this very study, the detection by means of bacteriologic data will result in high sensitivity, specificity, and negative predictive values (96.4%, 91.4%, and 99.9%, respectively) for deep SSI with no significant difference to the use of both types of data.

Cases are matched 1:1 to controls within each center by software provided by the coordinating center. Matching cases and controls within centers addresses the need for risk-adjustment to institutional characteristics and practices. Cases are matched to controls that received the same type of procedure. Individual pair-wise matching will be used, utilizing optimal matching to ensure the overall smallest possible Euclidean distance between cases and controls. Acknowledging the limited utility of using the National Healthcare Safety Network (NHSN) risk index, which only accounts for the existence of certain risk factors but not their composition, a propensity score is determined by logistic regression.

Costs are calculated by multiplication of the per-unit price for major cost drivers with the number of units used. Minor cost drivers, such as drug use, will be disregarded, as length of stay has been repeatedly shown to account for 90% of excess SSI costs [11].

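### The plain binomial 95% CI omits between-center variation, so the overall incidence interval (and those for large pooled categories or countries) is too narrow for a target beyond the 13 centers

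*Protocol article*

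**What the plan says.** The Statistical Analysis section plans country-level and institution-level rates by procedure and by surgical category, and continues: "For each incidence rate, the 95% CIs for a binominal proportion will be calculated". The Primary Analysis section sets the target as overall and procedure-specific incidence in Europe and adds: "The primary analysis will consist of calculating the incidence using 95% CIs". It names no interval method of its own.

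The precision statement is "incidence rates can be determined with a 95% CI of plus or minus 0.5% by observing 1500 surgical procedures", at an assumed rate of 1%. The case count uses 1.5% instead: "SSI of 1.5% in a population of 150,000, 2250 cases will be matched to 2250 controls".

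The Abstract lists 13 centers, "comprising 3 in France, 4 in Germany, 2 in Italy, 3 in Spain, and 1 in the United Kingdom". Under Study Sites, candidates are found through earlier SSI publications, earlier SSI studies and society membership, and are then selected by a feasibility questionnaire. Rationale and Principal Findings both carry the results over to the surgical population of Europe.

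Differences between centers are acknowledged twice. The Limitations paragraph under Methods accepts that procedures and documentation may vary by site. Principal Findings says of the case-control part: "Matching cases and controls within centers addresses the need for risk-adjustment to institutional characteristics and practices". The only other method named for rates is Poisson regression, in Further Statistical Evaluation. It is a sensitivity analysis with no stated center term.

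**The concern.** A binomial interval treats every patient as an independent draw from one population. Here patients come in about 13 blocks of roughly 10,000, and patients in a block share surgeons, prophylaxis, culturing habits and coding. If the true rate differs between centers, the precision of a rate meant to apply beyond them is governed mainly by the number of centers. Adding patients within a center cannot reduce that part of the error.

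The overall incidence is the first primary objective, and the article says the findings may inform vaccine trial design. A reader who takes an interval of about ±0.05 points as the uncertainty about Europe would be misled. The United Kingdom is the extreme case: with one center, its between-center variance cannot be estimated, and a binomial interval describes that hospital only.

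**Working it through.** **Inputs from the article:** rates of 1% and 1.5%; 1500 procedures; 90,000 to 150,000 patients; 13 centers split 3, 4, 2, 3 and 1.

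**Assumed:** equal center sizes; 130,000 patients (10,000 per center, in line with the minimum surgical volume under Study Sites); between-center CV of 10%, 20% or 50%. The article gives no CV or intraclass correlation (ICC).

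**1. The plan's own figure.** Half-width = 1.96 × √(p(1−p)/n) = 1.96 × √(0.01 × 0.99/1500) = 0.504 points. The stated ±0.5 reproduces with the independent-observation formula, so the sizing contains no design effect.

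**2. Overall rate at 1%.** Binomial SE = √(0.0099/130,000) = 0.0276 points, giving ±0.054. With center variation, SE_total = √(SE_b² + (CV × p)²/13), and the half-width is 2.179 × SE_total (t on 12 df). Coverage of the binomial interval = 2Φ(1.96 × SE_b/SE_total) − 1.

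| CV | SE_total (points) | Half-width | Ratio to ±0.054 | Binomial coverage |
|---|---|---|---|---|
| 10% | √(0.0276² + 0.0277²) = 0.0391 | ±0.085 | 1.6 | 83% |
| 20% | √(0.0276² + 0.0555²) = 0.0620 | ±0.135 | 2.5 | 62% |
| 50% | √(0.0276² + 0.1387²) = 0.1414 | ±0.308 | 5.7 | 30% |

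At 1.5% the binomial half-width is ±0.066. It becomes ±0.20 (CV 20%) to ±0.46 (CV 50%), with coverage of 54% to 25%.

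With unlimited patients, 13 centers at CV 10% still give 2.179 × 0.0277 = ±0.060, already wider than ±0.054.

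**3. Cross-check by design effect.** DE = 1 + (m − 1) × ICC, with m patients per center. An ICC of 0.001 at a 1% rate is a CV of about 31%. With 150,000 patients, m = 11,538 and DE = 12.5, so the effective sample is about 12,000 and coverage about 42%. At ICC 0.0001 (CV about 10%), coverage is 82% to 87% for 150,000 down to 90,000 patients. Using the 15 centers of the sizing text instead of 13 changes the widening little: 3.3 instead of 3.5 times at ICC 0.001 and 150,000 patients.

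**4. Country rates.** Four German centers would hold 4/13 × 150,000 ≈ 46,000 patients. At ICC 0.001, ±0.09 becomes ±0.09 × 3.54 = ±0.32 even with z; t on 3 df would widen it further. This is an all-surgery illustration. The article plans country rates by procedure and category, where cells are smaller and so is the design effect.

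**5. A procedure of 1500 spread over 13 centers.** m = 115.4, and ICC = (CV × p)²/(p(1−p)), which is 0.00040 at CV 20% and 0.0025 at CV 50%. DE = 1 + 114.4 × ICC = 1.05 to 1.29. With z, ±0.504 becomes ±0.515 to ±0.572. With t on 12 df the interval is 14% to 26% wider than binomial.

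**6. Concentrated or common procedures.** For 1500 patients in 3 centers, DE = 1 + 499 × ICC: 1.2 times wider at ICC 0.001 and 1.9 times at ICC 0.005. For 7500 patients over 13 centers (m = 577): 1.3 and 2.0 times. ICC 0.005 corresponds to a CV of about 70% at a 1% rate, which is a high assumption.

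**The case against.** **The method for the overall rate is inferred.** Primary Analysis asks only for 95% CIs, the binomial sentence follows one on country and institution rates, and an unseen analysis plan may say more. This stands as a caveat. But the sentence applies to every incidence rate, the sizing uses the same formula, and nothing shown points to another method.

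**The size is assumed.** This stands. The direction is certain wherever centers differ; the amount is not. A reader might take 30% or 62% coverage as a property of the plan, but the documents give no between-center variance, and the statement about matching concerns costs and outcomes, not how far incidence varies.

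**Procedure-specific rates are hardly affected.** A reader might infer that these intervals too are far too narrow. At the planned size of 1500 spread over all centers they are not. The problem grows only for common or concentrated procedures. For single institutions the binomial interval is appropriate.

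**The aim to show independence from procedure.** Background hopes to show that the "SSI rate is independent of the procedure performed and rather a consequence of cutaneous incisions". A reader might infer that overlapping procedure intervals would be offered as proof. The article does not say so, the aim is not among the listed objectives, and the matter is separate from clustering.

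**No interval makes purposive sites representative.** This stands. A center-aware interval repairs the width under a model in which these centers resemble a sample of similar ones. It does not guarantee 95% coverage for Europe, and methods for 13 clusters need small-sample care.

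**Conclusion.** The concern holds for the overall primary rate and, by the same mechanism, for large pooled categories and countries. Followed as written, the plan gives an interval that leaves out between-center variance while the stated target lies beyond the 13 centers. Over the assumed CV range of 10% to 50%, the overall interval should be about 1.6 to 5.7 times wider at a 1% rate. Even the low end costs about 12 points of coverage (83% against 95%). These figures rest on equal center sizes and the assumed CV; unequal sizes would raise the design effect. For procedures near 1500 patients in all centers the shortfall is modest. The point estimates are not affected.

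**What to change.** For the overall rate and every rate pooled over centers, replace the binomial interval with a center-aware one. Options are a logistic model with a random center effect, or a center-level interval using t with 12 df, in either case with a small-sample correction. If country enters as a fixed effect, 13 centers in 5 countries leave 13 − 5 = 8 df. Report the estimated between-center variance with the rate.

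Keep the binomial interval for single-institution rates. Present the United Kingdom figure as the result of one center, not as a country rate.

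The cost is a few sentences of analysis text, some code and a wider interval; no new data are needed. The text should say that the adjustment addresses width only and that bias from non-random site selection remains.

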#### Nested Case-Control Design

The nested case-control study generates data for analyzing costs and outcomes. Participants acquiring *S. aureus* SSIs will be documented in an electronic database and matched 1:1 to controls within each center. Criteria for matching are similar epidemiological data and procedure type, but without SSI and are specified in the Data Collection section.

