#### Secondary Analysis

The secondary analysis will consist of determining the overall and procedure-specific outcomes of *S. aureus* surgical site infections in Europe as well as the overall and procedure-specific economic burden of *S. aureus* SSI in Europe. Therefore, patients having established *S. aureus* SSI will be matched 1:1 to controls from the same center based on a propensity score and optimal matching with the following covariates: (1) type of procedure, (2) age, (3) ASA score, (4) BMI, (5) duration of procedure (as percentile for this procedure), (6) diabetes, and (7) sex.

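### Cases and controls are individually matched 1:1, but the named cost tests, bootstrap intervals and regression are not tied to the matched pairs

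*Protocol article*

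**What the plan says.** The design is paired, and the article says so three times. Under Nested Case-Control Design, cases are "matched 1:1 to controls within each center". Under Secondary Analysis, they "will be matched 1:1 to controls from the same center based on a propensity score and optimal matching", with type of procedure among seven covariates. Under Principal Findings in the Discussion: "Individual pair-wise matching will be used, utilizing optimal matching". The Rationale section gives the purpose of well-matched controls as estimating the incremental cost of SSI.

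The cost analysis is described under Statistical Analysis. Interval construction and similar analyses for costs "will be carried out using non-parametric bootstrap procedures". The association of major cost drivers and of overall costs with SSI occurrence "will be determined using bootstrapped t tests". Finally, "Multivariable regression analysis will be used to confirm significance of SSI occurrence for overall treatment costs". Costs are also to be stratified by depth of SSI. None of these sentences mentions pairs, within-pair differences, or clustering on the matched set.

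**The concern.** Testing an association between costs and SSI occurrence with a t test reads most naturally as a comparison of two groups, all cases against all controls. The data are not two independent groups. Members of a pair share center and type of procedure, and the Background section itself says that treatment cost depends on the prior procedure. Some positive within-pair correlation in cost is therefore plausible, at least in the overall comparison, where variation between procedures and centers is common to both members. An unpaired standard error counts that shared variation as noise.

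At stake is the precision of the excess-cost estimates. Overall and procedure-specific economic burden are two of the four secondary objectives. The depth-stratified costs raise the same issue in another way: a control has no SSI and so no depth, and can enter a depth stratum only through its matched case.

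**Working it through.** **Inputs.** Number of pairs: from Statistical Analysis. Confidence level 95%: from Further Statistical Evaluation. Within-pair cost correlation r and the cost SDs s1 (cases) and s2 (controls): not given in the article, so assumed and shown as a range.

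**The article's own figure.** 0.015 × 150,000 = 2250 cases matched to 2250 controls. This reproduces exactly. The question of pairing does not change it.

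**Effect on the standard error.** For n pairs:

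- paired: SE² = (s1² + s2² − 2·r·s1·s2)/n
- unpaired: SE² = (s1² + s2²)/n
- ratio unpaired/paired = √[(s1² + s2²)/(s1² + s2² − 2·r·s1·s2)], which is 1/√(1 − r) when s1 = s2
- actual two-sided error of a nominal 5% unpaired test = 2·[1 − Φ(1.96 × ratio)]

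Equal SDs:

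| r (cost scale) | SE ratio | Actual error | Actual coverage |
|---|---|---|---|
| 0 | 1.00 | 5.0% | 95.0% |
| 0.1 | 1/√0.9 = 1.05 | 3.9% | 96.1% |
| 0.3 | 1/√0.7 = 1.20 | 1.9% | 98.1% |
| 0.5 | 1/√0.5 = 1.41 | 0.6% | 99.4% |

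One SD three times the other:

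- r = 0.1: √(10/9.4) = 1.03, coverage 95.7%
- r = 0.3: √(10/8.2) = 1.10, coverage 97.0%
- r = 0.5: √(10/7) = 1.20, coverage 98.1%

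Only a negative r would make unpaired intervals too narrow (equal SDs, r = −0.1: coverage 93.8%).

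**Check with skewed costs.** Simulation of a bootstrap t test with no true difference: log-normal costs with log-scale SD 1, 200 pairs, 1000 runs, 399 resamples. Log-scale correlations of 0.2 and 0.5 correspond to cost-scale correlations of (e^0.2 − 1)/(e − 1) = 0.13 and (e^0.5 − 1)/(e − 1) = 0.38.

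| r (cost scale) | Rejection, patients resampled | Rejection, pairs resampled |
|---|---|---|
| 0 | 4.0% | 4.5% |
| 0.13 | 3.6% | 5.6% |
| 0.38 | 0.8% | 3.0% |

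At r = 0.38 the mean unpaired SE was 0.213 against an empirical SE of 0.168; the mean paired SE was 0.167. The ratio 0.213/0.168 = 1.27 agrees with 1/√(1 − 0.38) = 1.27.

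**Pairs per procedure.** A procedure with 1% of the volume has 150,000 × 0.01 = 1500 operations. At the two incidence rates used in the article, 1500 × 1% = 15 and 1500 × 1.5% = 22.5, so about 15 to 22 pairs. In simulations with similarly skewed costs and a case/control cost ratio of 1.6, a paired percentile bootstrap interval with about 20 pairs covered only about 88 to 89%. Pairing alone does not make such intervals reliable.

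**The case against.** The strongest reply is that the article never says unpaired. A bootstrapped t test can be run on within-pair differences, a non-parametric bootstrap can resample pairs, and such details often sit in the SAP, which is not shown. This stands in part. A reader might infer that the plan fixes a plain two-sample analysis that ignores the matching; the text does not support that. It does show that the article chose the test, interval method and regression by name, and that the wording most naturally describes two groups and ties none of the three to the pairs.

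A reader might also infer that the results would be misleadingly precise, or the excess cost biased. Neither follows. With positive within-pair correlation the error is conservative: false positives are not inflated. With complete pairs, the mean of the within-pair differences equals the difference of the group means, so the estimate does not move.

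Third, the correlation may be small. Propensity-score matching balances covariates across groups, and two patients with similar scores can still differ in age, BMI or duration; only center and type of procedure are clearly shared. At r = 0.1 the cost is about 5% in SE. With 2250 planned pairs, the overall estimate can bear a loss of that order. All of this stands and limits the size of the point. It does not remove it, because the remedy costs nothing.

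**Conclusion.** The point holds as a mismatch between a pair-matched design and a cost analysis not tied to the pairs. The consequence is lost precision, not lost validity: under positive within-pair correlation and patient-level resampling, intervals for excess cost are too wide and tests conservative. The loss in SE is about 5%, 20% and 41% at assumed cost-scale correlations of 0.1, 0.3 and 0.5 with equal SDs, falling to about 3%, 10% and 20% if one SD is three times the other. These sizes rest wholly on assumed correlations and SDs and apply only if patients, not pairs, are resampled. The primary incidence analysis is untouched. The change is worth making because economic burden is a secondary objective and its procedure-specific part has few pairs to spare.

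**What to change.** Add to Statistical Analysis:

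- The bootstrap resamples matched pairs, within center.
- The t tests and intervals for costs and cost drivers use within-pair differences. In strata by depth of SSI, each control enters through its matched case.
- The multivariable cost regression clusters on the pair or includes it in the model.

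Keep the procedure-specific cost results, since they are a stated secondary objective, and add a note that bootstrap intervals are unreliable where a procedure contributes few pairs (about 15 to 22 at 1% of volume). The cost is a few sentences of text and keeping the pair identifier in the analysis data set. No further data are needed, and neither the sample size nor the primary analysis changes.
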